#### Secondary study endpoints

2.5.2

Incidence and severity of adverse events among all treated subjects (evaluation indicators: Treatment toxicity graded according to CTCAE 5, Common Terminology Criteria for Adverse Events 5; overall survival (OS); objective response rate (ORR); In-field response to local radiotherapy; Distant response rate.

#### Exploratory study endpoints

2.5.3

1. Changes in the immunogenicity of tumor neoantigens before and after treatment, including changes in the immune response of immune cells to tumor neoantigens in peripheral blood before and after treatment. To detect neoantigen-reactive T cells, autologous PBMCs are collected from patients after vaccination and stimulated *in vitro* with their personalized neoantigen peptides. Neoantigen-specific T cell responses are then evaluated using interferon-γ (IFN-γ) enzyme-linked immunospot assay (ELISPOT) experiment to measure the changes in IFN-γ secretion upon neoantigen stimulation;2. The proportion of immune cells in the peripheral blood of patients before and after treatment. Here, makers including CD3, CD4, CD8, NK1.1 are detected by flow cytometry to screen neoantigen-specific T cells and efficacy markers;3. Analysis of changes in molecular or genetic indicators related to tumor response or progression before and after treatment. To enhance neoantigen specificity, peptide-MHC tetramers corresponding to predicted neoantigens will be prepared for patients with common HLA types, allowing for *in vitro* enrichment and characterization of neoantigen-specific T cells. scRNA-seq combined with TCR-seq is used to identify neoantigen-specific TCR sequences and analyze the diversification of neoantigen-specific TCR clonotype before and after treatment. If tumor tissue is available, both PBMCs and tumor tissue will be analyzed. In addition, ctDNA and TCR clonotype persistence are monitored, and epitope spreading of vaccine-induced T cell responses is also evaluated by analyzing the emergence or expansion of novel TCR clonotypes at different time points (pre-, mid-, and post-treatment) through TCR sequencing;4. When biopsy tissue is available, mIHC/IHC analysis can be used to observe changes in the immune microenvironment before and after vaccine treatment; memory T cell responses.

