17). Additionally, studies have shown that radiotherapy enhances tumor antigen presentation, boosts the variety of tumor-related antigens in draining lymph nodes, elevates T cell recruitment, and enhances the body’s ability to recognize and combat tumors (18, 19). Palma’s phase 2 SABR-COMET study (20) showed that stereotactic ablative radiotherapy (SABR) for metachronous oligometastatic advanced tumors significantly extended survival (41 *vs*. 26 months) but increased adverse reactions, though quality of life remained unaffected. Similarly, Gomez’s trial (21) on non-small cell lung cancer (NSCLC) with synchronous oligometastatic found that local consolidation radiotherapy greatly improved both survival (41.2 *vs*. 17 months) and progression-free survival (14.2 *vs*. 4.4 months). These clinical studies provide strong evidence supporting the effectiveness of local radiotherapy consolidation in advanced lung cancer. Our recent studies further investigated the dynamic changes in various types of immune cells and related factors during radiotherapy treatment. The data revealed that different radiotherapy doses and techniques have varying effects on both the tumor immune microenvironment (TIME) and the circulating immune system (STIE) (22). It is noteworthy that clinical data from large samples across different cancer types indicate that radiotherapy can lead to lymphopenia, which is associated with poor prognosis. Furthermore, alterations in immune factors like Transforming growth factor-beta (TGF-β) (23–25) and Indoleamine 2, 3-dioxygenase (IDO) (26) before and during radiotherapy are closely linked to tumor control and survival, showcasing the diverse patient responses to radiotherapy. Our previous personalized radiotherapy studies have shown that even under the same radiotherapy dose, different patients or tumors exhibit distinct responses to the same treatment regimen (27). For instance, Positron Emission Tomography-Computed Tomography (PET-CT) scans have revealed variations in tumor regression and normal organ damage among patients, illustrating the heterogeneous tumor response to treatment (28). Additionally, we observed that the volume factor, which refers to the changes in tumor volume during treatment, had significant effect on survival, highlighting how treatment response heterogeneity influences the final treatment outcome (29). By utilizing biological metabolic imaging to guide FDG-PET mid-treatment response and employing adaptive radiotherapy technology (BigART) to tailor treatment for stage III NSCLC patients undergoing concurrent chemotherapy, we have demonstrated that optimizing individual doses, enhancing tumor dose delivery, and protecting normal tissues through BigART can ultimately enhance tumor control and prolong survival (30, 31). Multi-center clinical trials have confirmed the aforementioned findings, and we presented the results of RTOG1106 at the 2020 World Lung Cancer Congress (32). Our study achieved the highest ranking in Phase III trials. Recognizing the variability in individual responses to radiotherapy and the potential for toxic side effects, we propose a novel approach known as critical lesion eliminating radiation therapy (CLERT) for stage IV patients. This method follows isotoxicity planning and adheres to radiation dose limits outlined in the NCCN guidelines for organs at risk (OAR), with a dosage limit set at 80% of the recommended level. By implementing precise and personalized radiotherapy, our aim is to optimize therapeutic outcomes while minimizing damage to both the local and systemic immune microenvironments.

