**Figure 1 f1:**
[figure not shown]
Flowchart of the study design.

**Control group:** placebo + conventional treatment (including radiotherapy) group,

**Intervention group:** personalized tumor peptide vaccine + conventional treatment (including radiotherapy) group,

Subjects will be stratified according to different cancer types and first, second, and third-line treatment stages based on individual condition assessment, and then randomly enter two cohorts in a 1:1 ratio. In addition, there is a one-way crossover experiment (cross-over design) during the research process. Cross-over to the investigational treatment arm (peptide vaccine plus radiotherapy) will be permitted only for patients in the control group who demonstrate radiologically confirmed disease progression, as assessed by RECIST 1.1 and verified by the investigator. Eligibility for cross-over requires that patients meet predefined safety and clinical criteria, including an ECOG performance status of ≤2, absence of Grade ≥3 adverse events, and adequate hematologic, hepatic, and renal function. The proportion, timing, and reasons for cross-over will be systematically recorded and transparently reported. The intervention group will undergo the second phase of personalized tumor peptide vaccine group plus conventional treatment (including radiotherapy), and the response rate of the two phases will be evaluated before and after crossover. In both cohorts, all subjects received radiotherapy, and radiotherapy doses will be further divided into low and high doses. This design will allow us to answer questions about vaccination efficacy and the impact of various radiation doses.

For patients who want to enroll in neoantigen clinical trials, screening for neoantigens may be recommended. It is necessary to take the patient’s fresh tumor tissue (surgery or biopsy or cerebrospinal fluid, pleural effusion, ascites, etc.), and perform whole-exome and whole- transcriptome sequencing on peripheral blood for further clinical development of individualized targeted treatment plans. At the same time, these test data can be used for personalized tumor neoantigen screening in this study. Peptide vaccine therapy requires an 8-week preparation period for the preparation of the peptide vaccine, during which patients continue to maintain standard treatment.

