### Treatment methods

2.3

This study includes personalized neoantigen peptide vaccine treatment and precision radiotherapy. The treatment sequence is radiotherapy first and then vaccine (**Figure 2**). The interval between precision radiotherapy treatment and peptide vaccine is 1 week.

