#### Precision radiotherapy

2.3.1

The course of treatment is 1 week, 3 times in total.

1. Critical lesion eliminating radiation therapy CLERT, in accordance with isotoxicity planning, radiation dose limits are based on standard NCCN (National Comprehensive Cancer Network) guidelines recommended for organs at risk (Organs at risk, OAR) limit dosage to 80% formulation.2. Critical lesions (Critical lesions) are defined as tumors in critical locations. If the tumor progresses in this location, it will lead to the patient’s death or severe symptoms, affecting the patient’s QOL (the quality of life). Life-threatening tumors such as: central lung cancer; tumors adjacent to large blood vessels, large tracheas, heart, esophagus and other mediastinal tumor lesions; metastatic tumors located in or adjacent to the brainstem. Situations that seriously endanger QOL include, but are not limited to, the following situations: tumors are in the spinal cord, esophagus, portal area, and load-bearing bones, or are close to the rectum, bladder, etc. The final decision was made by a panel of on-study radiation therapy experts.3. Radiotherapy, SBRT (stereotactic body radiation therapy), the protocol is 8–10 Gy × 3 versus 2 Gy × 3. The radiation dose limit is based on 80% of the OAR limit dose recommended by the standard NCCN guidelines. If the metastases are close to important structures such as the brainstem or esophagus, or have been previously treated with radiotherapy, the radiation dose limit allows the SBRT radiation dose to be adjusted to the OAR guideline limit dose.4. The key tumor is the treatment target area, which refers to the tumor tissue that mainly affects or threatens the patient’s life or QOL, regardless of the primary site or metastasis, as mentioned above. EDIC (The effective dose to the circulating lymphocyte EDIC, the equivalent dose of circulating lymphocytes) is an important reference indicator for formulating radiotherapy plans. The EDIC is limited to an effective dose that produces grade 2 or higher lymphocyte deficiency in less than 5% of patients. (Patented, part of the research data was disclosed by [name]/[name], et al. in ASTRO2017).

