### Follow-up

2.6

At the end of each course of treatment, patients must return to the hospital for a visit. If necessary and the patient wishes, the trial procedure for the next course of treatment can be started. At the same time, visits must be made every 3 months after each course of treatment. Visits and examinations include blood routine, blood biochemistry, urine routine, stool routine, and coagulation function test on accompanying medications. Carcinoembryonic antigen (CEA) and other tumor markers, CD antigen, T cell activity assessment, vital signs, ECOG score, electrocardiogram, imaging examination (CT, MRI). Please refer to the visit plan for details of the visit plan (**Table 1**). When a certain assessment is required, a “ √ ” will be marked on the visit plan.

**Table 1 T1:** Visit reporting table.

Item	The end of treatment	Post-treatment visit (every 3 months)
Concomitant medication	✓	✓
Blood routine	✓	✓
Blood chemistry	✓	✓
Urine routine	✓	✓
Bowel routine	✓	
Coagulation function test	✓	
Thyroid function test	✓	
Alpha-fetoprotein	✓	
Pregnancy test	✓	
Vital signs	✓	✓
Physical examination	✓	✓
ECOG score	✓	✓
Electrocardiogram	✓	
Echocardiogram	✓	
Blood pressure detection	✓	
Film degree exam	✓	

The follow-up plan lasts for 24 months and is divided into 8 times, that is, every 3 months after the end of treatment, 10 mL of blood will be collected each time for efficacy and safety evaluation, while compliance will be assessed and combined medication status will be recorded.

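### Exploratory endpoint item 2 (2.5.3) follows blood immune cells as proportions across radiotherapy, so lymphocyte loss can look like expansion or go unseen; absolute counts should be reported beside them

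*Protocol article*

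**What the plan says.** Section 2.5.3, item 2 of the protocol article gives the measure as "The proportion of immune cells in the peripheral blood of patients before and after treatment". The markers are CD3, CD4, CD8 and NK1.1, and they "are detected by flow cytometry to screen neoantigen-specific T cells and efficacy markers". No absolute count is named there or in section 2.9, item 6, which lists flow cytometry among the methods for neoantigen response.

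Four other places bear on how this measure reads:

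- **Exposure (2.2 and 2.3).** "In both cohorts, all subjects received radiotherapy, and radiotherapy doses will be further divided into low and high doses". "The treatment sequence is radiotherapy first and then vaccine".
- **Known effect (Introduction).** "radiotherapy can lead to lymphopenia, which is associated with poor prognosis". The same section says that radiotherapy doses and techniques differ in their effect on the circulating immune system.
- **Planning limit (2.3.1, item 4).** "The EDIC is limited to an effective dose that produces grade 2 or higher lymphocyte deficiency in less than 5% of patients".
- **Blood tests (2.6).** "Visits and examinations include blood routine, blood biochemistry, urine routine, stool routine", and further on "CD antigen, T cell activity assessment, vital signs, ECOG score". Table 1 places the blood routine at the end of treatment and at each 3-monthly visit after it, and has no pre-treatment column.

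**The concern.** The endpoint is fixed on a relative scale, and the interval it spans contains an exposure that the protocol itself links to loss of lymphocytes. The share of a subset depends on its own number and on the number of everything else in the denominator. If the rest falls more, the share rises although no cell has been gained. If everything falls alike, the share stays put and the loss does not show.

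Two readings are at stake. The first is the within-patient change, which item 2 uses to look for efficacy markers. The second is the comparison of high with low dose: section 3.1 says the dose subgroups exist to explore how dose modulates immunity. If one dose depletes lymphocytes more, it may look the more immune-activating on proportions alone. Random allocation to dose does not cure this, because depletion is itself an effect of dose. Adverse-event records may not reveal the loss either, since section 2.7.1 generally does not count an abnormal laboratory value alone as an adverse event.

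**Working it through.** The plan gives no figure to reproduce here. The check is whether a share can mislead in the way described, and by how much.

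**Inputs.** From the article: the scale is a proportion; radiotherapy falls between the two samples; every patient receives it. Not in the article, and therefore assumed: the size of the loss and how it spreads across subsets.

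**Formula.** Let T be the fraction of all lymphocytes lost and S the fraction of the subset lost, both as they stand when the second sample is drawn. Then

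share after / share before = (1 − S) / (1 − T), and count after / count before = 1 − S.

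The share rises whenever S < T, even though the count falls.

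| Assumed T | Assumed S (CD8) | Share ratio | Change in share | Change in count |
|---|---|---|---|---|
| 30% | 20% | 0.80/0.70 = 1.14 | +14% | −20% |
| 50% | 35% | 0.65/0.50 = 1.30 | +30% | −35% |
| 60% | 40% | 0.60/0.40 = 1.50 | +50% | −40% |
| 40% | 40% | 0.60/0.60 = 1.00 | 0% | −40% |
| 20% | 30% | 0.70/0.80 = 0.875 | −12.5% | −30% |

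The first three rows have the wrong sign. The fourth hides the loss. The fifth, where CD8 cells are lost more than the rest, has the right sign but understates the fall.

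**Check with explicit counts.** Assumed baseline per µL: CD4 800, CD8 450, B 250, NK 200; total 1700; CD8 share 450/1700 = 26.5%.

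- Mild uneven loss (CD4 20%, CD8 10%, B 40%, NK 10%): total 640 + 405 + 150 + 180 = 1375. CD8 share 405/1375 = 29.5%, a relative rise of 11%; CD8 count down 10%.
- Moderate loss (40%, 25%, 70%, 20%): CD8 count 450 to 338, down 25%; share 32.1%, up 21%.
- Severe loss (60%, 45%, 80%, 40%): CD8 count 450 to 248, down 45%; share 33.6%, up 27%.

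Multiplying the share by the lymphocyte total returns the true count: in the mild case, 0.2945 × 1375 = 405.

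**Dose comparison.** Suppose the second row of the table held at one dose and the first row at the other. The more depleting dose would show a CD8 share higher by a factor of 1.30/1.143 = 1.14, while its CD8 count would be lower by a factor of 0.65/0.80 = 0.81. The two scales would rank the doses in opposite order.

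**Recovery.** If half of the loss in the first row had recovered by the time of sampling (T = 15%, S = 10%), the ratio would be 0.90/0.85 = 1.06, an apparent rise of 6%.

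**The case against.** The strongest reply is that this is an exploratory endpoint named in one sentence of a condensed article. It gives no gate or denominator and does not say that counts will be left out, so the full protocol or a laboratory manual may supply them. That is fair for the gate. It does not dispose of the point, because the scale itself is stated, and it is the relative one.

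Several further objections stand and set the limits:

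- **Immune monitoring is wider than item 2.** A reader might infer that all of it is relative. The documents do not support that: ELISPOT, tetramers and TCR sequencing are separate measures, and the CD antigen test in section 2.6 has no stated unit, so it may be a count.
- **The sign is not bound to reverse.** Reversal needs the subset to be lost less than the total, and nothing in the article says that this holds for CD8 cells. The loss sizes have no source in the document. The planning limit in section 2.3.1 is meant to keep deficiency of grade 2 or higher below 5% of patients, though it leaves milder loss open. Radiotherapy takes one week and the vaccine course about five months, so a sample at the end of treatment may come after much recovery.
- **The correcting counts are not shown to be in hand.** A reader might take the blood routine to settle this at no cost. Table 1 shows neither a pre-treatment count nor a lymphocyte differential, and no pairing with the flow sample.
- **The multiplication is not valid for every gate.** A share of CD3+ cells or of PBMCs, times the lymphocyte count, gives a wrong number. CD3, CD4 and CD8 also overlap, so the listed markers need not sum to 100%; the argument needs only a common denominator.
- **The dose analyses are declared hypothesis-generating** in section 2.8. Nothing in the article shows a primary or secondary endpoint, or a decision in the trial, resting on item 2.

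**Conclusion.** The point holds for item 2 of section 2.5.3. Reported alone, the proportion cannot distinguish expansion from uneven loss and cannot show uniform loss, across an exposure that the protocol says can deplete lymphocytes. On the assumed losses, the CD8 share rises by 11% to 50% while the count falls by 10% to 45%. These figures show the mechanism and are not a forecast. The true size is unknown and may be modest, given the planning limit and the time for recovery.

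The before/after reading and any high- versus low-dose comparison of these cells are affected. One might infer that the vaccine effect or the main result is compromised, but the documents do not support that. Both arms receive radiotherapy at the same two dose levels, so the distortion largely cancels between vaccine and control, and progression-free survival does not use this measure. Nor is there reason to drop the proportion, which remains informative about composition. What is missing beside it is the count.

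**What to change.** In section 2.5.3, item 2, add the absolute count of each subset beside its proportion, defined as

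count = (subset as a share of total lymphocytes) × (lymphocyte count from the same-day blood routine).

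State that the flow gate is expressed on total lymphocytes. Where a subset is gated on CD3+ cells, multiply first by the CD3 share of lymphocytes. Add that any claim of expansion, or of a difference between high and low dose, will rest on both scales.

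The cost is a few lines of wording and a matched blood draw. The one thing to settle is the baseline: confirm that a count with differential is taken before radiotherapy on the same day as the first flow sample, since Table 1 of the article shows the blood routine only at the end of treatment and every 3 months after. It should be settled prospectively, because a missing same-day count cannot be recovered later. For patients already enrolled without one, only the proportion can be reported, and it should be labelled as such.

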
Combining radiotherapy and immunotherapy has the potential to enhance both innate and adaptive immunity, ultimately improving patient survival rates. This suggests a potential of synergetic effect with neoantigen vaccines. The immunomodulatory effects of radiotherapy deponed upon various factors such as dose, fractionation, and timing (33). High-dose radiotherapy (HDRT) with doses exceeding 8Gy (33, 34) enhances tumor recognition by T cells, promoting immunogenic cell death (ICD) (34) and T cell activation (35), but also increases regulatory T cells (Tregs) (36) and myeloid-derived suppressor cells (MDSCs) (37–39). HDRT can trigger systemic anti-tumor immunity and synergizes with immune checkpoint blockade (39). Low-dose radiotherapy (LDRT) with doses below 2Gy (33), though less directly tumoricidal, reshapes the tumor microenvironment, suppresses Tregs, MDSCs and rebalances TH1/TH2 (40), and maximizes immunomodulatory effects (activation of dendritic cells (DCs), T cells, NK cells, and B cells) (41) with lower toxicity, enabling multi-site irradiation (41, 42). Various regimens exist in the clinic, with LDRT paired with HDRT, chemotherapy, or immunotherapy for enhanced tumor control (43). Research on radiotherapy combined with neoantigen vaccines remains limited. A preclinical mouse study in 2020 demonstrated that radiotherapy induced the release of neoantigens, which when combined with neoantigen vaccines, led to the expansion of neoantigen-specific CD4+T cells and CD8+T cells, significantly enhancing the anti-tumor effect (18). While these findings are encouraging, it is important to note that results from mouse models do not always translate directly to humans, particularly in advanced cancer stages. Additionally, a clinical trial evaluating the combination of personalized neoantigen vaccines and radiotherapy has been registered in the United States (NCT02287428), although its results have not yet been published. Collectively, these studies suggest (1) Radiotherapy can upregulate the expression of genes containing immunogenic mutations. This means that radiotherapy can increase the visibility of neoantigens to the immune system; (2) Neoantigen-specific CD8+ T cells preferentially kill irradiated tumor cells. This cytotoxic activity relies on the ability of radiation to upregulate class II MHC molecules as well as the death receptors FAS/CD95 and DR5 on the surface of tumor cells. (3) Combining neoantigen vaccines with radiotherapy and chemotherapy might achieve better therapeutic effects. This is because the combination can help overcome immunosuppression in the tumor microenvironment and optimize neoantigen presentation to the immune system. This provides a theoretical foundation for further exploration of neoantigen vaccine combined with radiotherapy.

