### Statistical methods and data analysis

2.9

1. The results of this experiment mainly use statistical description methods. The measurement data lists the mean, standard deviation, median, maximum value, and minimum value, and the technical data and grade data list the frequency, rate, and confidence interval.2. All statistical analysis will be performed using SPSS software.3. Safety analysis: Mainly descriptive statistical analysis, analyzing adverse events, serious adverse events and adverse reactions of each group of people. Adverse reactions are defined as “definitely related/possibly related, unable to determine” related to this clinical trial.4. Survival Analysis: Progression-free survival (PFS), the primary endpoint of this study, will be analyzed based solely on data collected prior to cross-over, thereby preserving the integrity and statistical power of the comparison between neoantigen and placebo groups. The Kaplan-Meier method will be used to estimate the median PFS and calculate 95% confidence intervals. Group differences will be compared using the log-rank test. Overall survival (OS), as a secondary endpoint, will be estimated using Kaplan-Meier curves and log-rank tests. To account for potential bias introduced by the cross-over design, we will apply the rank preserving structural failure time (RPSFT) and two-stage methods, as well as inverse probability of censoring weighting (IPCW) to adjust for treatment switching. Additionally, adjusted OS analyses will be conducted by matching patients who cross over with comparable patients in the vaccine group based on key baseline factors (e.g., cancer type, age, performance status), using propensity score matching or multivariable Cox proportional hazards modeling. Sensitivity analyses will include intention-to-treat (ITT), per-protocol, and as-treated populations. Subjects will be stratified according to cancer type and first, second, and third-line treatment stages based on individual condition assessments, ensuring that these factors are appropriately considered in the analysis. Additionally, in the multivariable Cox proportional hazards model for both PFS and OS, cancer type will be included as a covariate, along with other relevant baseline factors, to control for potential confounding effects.5. Other Effectiveness analysis: Estimate the objective response rate (ORR), disease control rate (DCR) and other efficacy endpoints and improve the 95% confidence interval. The interval estimation uses the Clopper-Pearson method. The effect of lab correlates such as RT dose on clinical outcomes of response and time-to-event will be estimated using logistic regression and Cox mode respectively. The longitudinal data such as quality of life will be estimated using mixed-effect model.6. Tumor neoantigens response analysis: Neoantigen-specific responses are evaluated by ELISPOT, flow cytometry, and TCR-seq. Peptide–MHC tetramers enrich specific T cells for scRNA/TCR-seq analysis in PBMCs and tumor tissue (if available). TCR clonotype dynamics, ctDNA, and epitope spreading are monitored over time. IHC/mIHC is used to assess immune microenvironment changes when biopsy samples are available.

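### The flow markers named for patients' blood in section 2.5.3 item 2 include a mouse NK marker and no marker of antigen specificity, although the item says they screen neoantigen-specific T cells

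*Protocol article*

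**What the plan says.** Section 2.5.3 of the protocol article lists the exploratory endpoints. Three of its items bear on this point.

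- **Item 1** covers the response of immune cells to neoantigens. PBMCs are "stimulated *in vitro* with their personalized neoantigen peptides" and read by IFN-γ ELISPOT.
- **Item 2** is defined as "The proportion of immune cells in the peripheral blood of patients before and after treatment". Its method sentence reads: "makers including CD3, CD4, CD8, NK1.1 are detected by flow cytometry to screen neoantigen-specific T cells and efficacy markers". No other marker is named for this item, and neither tetramers nor peptide stimulation is mentioned in it.
- **Item 3** turns to specificity: "peptide-MHC tetramers corresponding to predicted neoantigens will be prepared for patients with common HLA types". These are used with scRNA-seq and TCR-seq.

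The analysis section, 2.9 item 6, says: "Neoantigen-specific responses are evaluated by ELISPOT, flow cytometry, and TCR-seq". Its next sentence mentions tetramers, as a way to enrich cells for scRNA/TCR sequencing.

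NK cells also appear in the trial's rationale. The Introduction lists among the effects of low-dose radiotherapy the "activation of dendritic cells (DCs), T cells, NK cells, and B cells".

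**The concern.** Two things in item 2 do not fit together.

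First, the samples are human and NK1.1 is a mouse marker. If a laboratory followed the text literally, the NK proportion before and after treatment would carry no information. NK activation is one of the effects the Introduction attributes to low-dose radiotherapy, and the trial contrasts low with high dose. An NK readout that works would therefore be of use.

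Second, CD3, CD4 and CD8 identify a T cell's lineage and subset whatever antigen it recognises. A panel of these markers cannot screen for neoantigen-specific cells. Section 2.9 item 6 then lists flow cytometry among the methods for neoantigen-specific responses without saying how the flow readout is made specific. This leaves room for a shift in bulk CD4 or CD8 to be read as a vaccine response. Item 2 is a before-and-after comparison, radiotherapy precedes the vaccine (section 2.3), and the Introduction itself says that radiotherapy can cause lymphopenia and that its effect on circulating immunity varies with dose. A bulk shift therefore has an obvious explanation other than the vaccine.

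**Working it through.** No arithmetic applies: the documents give no figure for this endpoint, and the point depends on no sample size, event count or error rate. The check sets the named markers against the two tasks that item 2 gives them, and then against the neighbouring text.

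**Inputs.** The marker list, sample type and stated purpose come from section 2.5.3 item 2. The specificity methods come from items 1 and 3. The analysis wording comes from section 2.9 item 6. What each marker identifies is standard immunology nomenclature; the protocol does not state it, and the point rests on it.

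**Task 1: proportions of immune cells in human blood.**

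- CD3 identifies T cells: suitable.
- CD4 and CD8 identify the main T-cell subsets: suitable.
- NK1.1 identifies NK cells in mice. Human NK cells are conventionally gated as CD3-negative and CD56/CD16-positive: not suitable.

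Three of the four named markers do this task. The one named for NK cells does not, and no other NK marker is named.

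**Task 2: screening neoantigen-specific T cells.**

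- CD3, CD4 and CD8 are carried by T cells of the class regardless of antigen: no specificity.
- NK1.1 is not a marker of T-cell antigen specificity in any case.

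None of the four does this task alone. CD3, CD4 and CD8 would contribute only as gating markers alongside a specificity step.

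**Against items 1 and 3.** Each of these supplies the missing step: the patient's own peptides in item 1, tetramers in item 3. Item 2 names neither. The section thus treats specificity as needing a dedicated reagent or stimulation in two places and assigns it to lineage markers in the place between them.

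**Against section 2.9 item 6.** Flow cytometry is listed as a readout of neoantigen-specific response. Tetramers are named in the following sentence, where their stated use is enrichment before sequencing. The two sentences can be read together as tetramer-gated flow, but the text does not say so.

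**The case against.** The case on the other side is substantial, and much of it stands.

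- **The marker list is open.** It is introduced by a word that makes it illustrative, and a journal article commonly leaves full panels and gating to the full protocol or laboratory manual. This stands. A reader might infer that the panel holds lineage markers only and can measure neither human NK cells nor specific T cells. The document does not support that; the point reaches only the markers named. An open list does not, however, make NK1.1 a human marker.
- **CD3, CD4 and CD8 serve the endpoint as defined.** This stands for T-cell subset proportions. It does not rescue the added purpose of screening specific cells.
- **Specificity is measured elsewhere.** This stands. ELISPOT covers it in item 1, and tetramers with TCR-seq cover it in item 3 for patients with common HLA types. A reader might infer that the trial cannot detect neoantigen-specific T cells; the same section shows otherwise.
- **Section 2.9 item 6 can be read with the tetramers it names.** This stands as a possible reading, so that sentence is better called unclear than wrong. One clarifying clause settles it.
- **The harm is conjectural.** A reader might infer that bulk CD4 or CD8 changes will be reported as neoantigen-specific responses. Nothing says they will be; the wording only permits it. Radiotherapy is given in both arms, so its effect alone should not produce a difference between them. That protects the randomised comparison, but not a before-and-after reading.
- **NK1.1 may be a slip of naming.** This is plausible, and the document cannot settle it. A slip in the endpoint text still needs correcting, because laboratories may work from that text.
- **No NK endpoint is listed separately.** True. NK cells enter only through this marker and the general endpoint on immune-cell proportions, which limits the importance of the point.

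**Conclusion.** The point holds for the markers as named. NK1.1 gives no valid NK proportion in human blood, and it is the only NK marker given. CD3, CD4 and CD8 give subset proportions but no antigen specificity, so the stated purpose of screening neoantigen-specific T cells does not follow from the named markers. The conclusion rests on standard marker nomenclature and on the written text; it makes no claim about a fuller panel that is not shown.

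The size is small and cannot be put as a number. The documents give neither the frequency of specific cells nor the variation of CD8 under radiotherapy, and a share of the panel has no denominator while the list is open. The impact is confined to one exploratory endpoint. PFS, the sample size, safety, ELISPOT and TCR-seq are unaffected. It is still worth correcting before the samples are analysed, because NK data acquired without a human NK marker might not be recoverable.

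**What to change.** 1. In section 2.5.3 item 2, replace NK1.1 with a human NK definition, for example CD3-negative, CD56/CD16-positive cells.
2. In the same item, limit this panel to reporting immune-cell proportions. Delete the purpose of screening neoantigen-specific T cells, or tie it expressly to tetramer gating or to gating after peptide stimulation.
3. In section 2.9 item 6, state that flow cytometry counts as a neoantigen-specific readout only with such gating.

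The cost is one antibody change, if the laboratory does not already use a human marker, and wording changes in two places. No extra patients, visits or blood samples are needed. If the laboratory documents already specify a human NK marker and specificity gating, aligning the text is enough.
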